**Fig. 1 Fig1:**
[figure not shown]
Flowchart of the study CONSORT

### Eligibility criteria

All registered students at the University of Minnesota will be potentially eligible to participate. Eligibility criteria include being at least 18 years of age and self-reporting mild to severe symptoms of depression (5–27+) on the Patient Health Questionnaire-9 (PHQ-9; [26, 50]), mild to severe symptoms of anxiety (5–21+) on the Generalized Anxiety Disorder (GAD-7; [49]), or mild to severe symptoms of stress (15–34+) on the stress subscale of the Depression, Anxiety and Stress scale-21 (DASS-21; [28]). Students who score below the cutoff score on a given measure may still use the program module related to that measure, although their data will not be included in the analyses. Participants attending face-to-face individual or group counseling will be excluded. This includes all types of psychological therapy such as CBT. At baseline and 3 month assessments, participants will be asked if they have accessed any other form of psychological intervention throughout the time frame of the trial.

Students who score in the “red zone” in terms of risk of self-harm on the screening questions routinely used at SCS (i.e., the Behavioral Health Measure; [6]) will not be referred to the study. Students who score greater than 0 on the PHQ-9 self-harm item in the online screening will be automatically alerted that a counselor will try to reach them. They will be recommended to seek help from BMHC or UCCS. They will be telephoned within 1 working day and contacted by email if they cannot be reached by phone. There is also a “Help” button available on the site which can be accessed at any time and which directs students to a list of counseling resources and health services on campus.

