### Recruitment procedure

Participants will be recruited through three units at the University of Minnesota-Twin Cities, a public research university located in Minneapolis and St. Paul, Minnesota. The first unit is Student Counseling Services (SCS) which provides free short-term counseling to undergraduate and graduate students. The second is Boynton Mental Health Clinic (BMHC) which also provides short-term psychological services to full-time students at the University of Minnesota. Unlike SCS, BMHC also has psychiatrists on staff and is affiliated with the university health service. Finally, we will recruit participants through the International Student and Scholar Services (ISSS) office which provides counseling to foreign national students on campus.

The SilverCloud programs will be advertised to students through the three participating offices on campus via staff referrals, brochures, flyers, email announcements, and web sites and through the general student mental health web site. Regardless of how they learn about the programs, students can sign up online to get access to the programs. If a student expresses interest, they will be emailed a link to a web site with more information about the programs and the study. Interested students will sign the consent form and complete screening measures online and will be given feedback on their scores. This feedback consists of informing students of their overall score for each measure and whether their score indicates mild, moderate or severe depression, anxiety, or stress. This will allow them to make an informed decision on choosing one of the three programs. They will then be referred to a supporter from within the service where they learned about the study. Participants’ post outcome measures will be gathered 8 weeks after their initial log in or activation of the program and 3 months later (5 months after initial log in).

A second recruitment phase will be conducted at 3-month follow-up. All 105 participants will be contacted by email and invited to complete a semi-structured interview about their perceptions, attitudes, and experiences of the intervention. From those that respond expressing an interest, the first 25 will be selected to complete a semi-structured interview.

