### Symptom outcome measures

The PHQ-9 [26, 50] is a 9-item self-report measure of depression that has been widely used in screening, primary care, and research. The PHQ-9 items reflect the diagnostic criteria for depression outlined in the *Diagnostic and Statistical Manual of Mental Disorders, Fourth Edition–Text Revision* (DSM–IV–TR) [3]. Items are rated on a 0 to 3 scale. Summed scores range from 0 to 27; higher scores reflect a greater severity of depressive symptoms [26, 50].

The GAD-7 [49] comprises 7 items measuring symptoms and severity of GAD based on the DSM-IV diagnostic criteria for GAD. The GAD-7 has good internal consistency (.89) and good convergent validity with other anxiety scales. Items are rated on a 0 to 3 scale. Summed scores range from 0 to 21; higher scores indicate greater severity of symptoms [49].

Stress subscale of Depression, Anxiety and Stress scale-21 (DASS-21). The DASS-21 [28] is an abbreviated version of the original 42-item DASS. It is composed of three 7-item subscales measuring symptoms of depression, anxiety, and stress. Participants will be asked to rate the degree to which they endorse each of the seven stress items on a 4-point scale (0 to 3). Summed scores range from 0 to 21; higher scores indicate greater severity of symptoms. Scores on the DASS-21 have been found to be valid measures of depression, anxiety, and stress in non-clinical samples [17].

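### The DASS-21 stress cut-off (15–34+) and the stated 0–21 scoring of the same subscale cannot be on one metric, so the stress analysis set is not defined

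*Protocol article*

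**What the plan says.** Three places in the protocol article bear on this.

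- **Eligibility criteria.** Stress entry requires "mild to severe symptoms of stress (15–34+) on the stress subscale". The companion criteria are "mild to severe symptoms of depression (5–27" and "mild to severe symptoms of anxiety (5–21" (each also printed with a plus sign), and the three are alternatives. A student below the threshold on a measure "may still use the program module related to that measure, although their data will not be included in the analyses".
- **Symptom outcome measures.** For DASS-21 stress, participants rate "each of the seven stress items on a 4-point scale (0 to 3). Summed scores range from 0 to 21". The DASS-21 is described there as a shortened form of a 42-item instrument. No doubling or other rescaling of the sum is mentioned, here or elsewhere.
- **Recruitment procedure.** Before choosing a program, students are told their score on each measure and "whether their score indicates mild, moderate or severe depression, anxiety, or stress". The cut-points behind those labels are not given.

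**The concern.** The two sections give figures for the same subscale that cannot both hold. This is more than a slip in a descriptive sentence, because the threshold determines whose stress data are analysed.

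If 15 were applied to the 0–21 sum, students with lower stress scores could use Space from Stress but would not count in its analysis. The SD and the within-group Cohen's d would then describe a narrow upper band. The Objectives, Sample size and Planned statistical analysis sections all intend these estimates to inform a future RCT. Selecting on a high baseline value in a study with no control group also enlarges the part of the change that is regression to the mean.

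**Working it through.** **Inputs.** Seven items, each 0–3, stated range 0–21 (Symptom outcome measures). Cut-off bands 15–34+ for stress, 5–27+ for PHQ-9, 5–21+ for GAD-7 (Eligibility criteria). Target 35 per group (Sample size).

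**1. Reproduce the stated range.** Maximum = items × top response = 7 × 3 = 21. The stated range is correct for a plain sum.

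**2. Compare each band with its scale.**

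| Measure | Maximum | Band | Upper figure minus maximum | Lower bound / maximum |
|---|---|---|---|---|
| PHQ-9 | 9 × 3 = 27 | 5–27+ | 0 | 5/27 = 19% |
| GAD-7 | 7 × 3 = 21 | 5–21+ | 0 | 5/21 = 24% |
| DASS-21 stress | 7 × 3 = 21 | 15–34+ | 34 − 21 = 13 | 15/21 = 71% |

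The other two bands end exactly at their scale maxima, so loose use of the plus sign does not explain the stress band.

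**3. Literal reading: 15 on the 0–21 sum.** Qualifying scores are 15 to 21, that is 7 of 22 values (32%). The lowest needs a mean item score of 15/7 = 2.14 out of 3.

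**4. Alternative reading: a rescaled sum.** The smallest whole-number multiplier that makes 34 attainable is 2, since 34/21 = 1.62, giving 0–42. Then 15/2 = 7.5, so sums of 8 to 21 qualify, 14 of 22 values. The two readings differ on sums 8–14. In the other direction, a plain sum of 15 becomes 30, which lies (30 − 15)/(34 − 15) = 79% of the way up the printed band.

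**5. Effect on the baseline SD.** An SD (divisor n) cannot exceed half the range of the data. For 15–21 the ceiling is (21 − 15)/2 = 3; for 8–21 it is (21 − 8)/2 = 6.5. This needs no distributional assumption.

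**6. Illustration of numbers.** The documents give no stress distribution. Assume the plain sum among screened students is normal with mean 7–13 and SD 4–5, with a continuity correction (cuts at 14.5 and 7.5).

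| Mean, SD | P(≥15) | P(≥8) | Ratio | Screened for 35: cut 15 / cut 8 |
|---|---|---|---|---|
| 7, 4 | 0.030 | 0.450 | 0.068 | 1152 / 78 |
| 9, 5 | 0.136 | 0.618 | 0.220 | 258 / 57 |
| 11, 4 | 0.191 | 0.809 | 0.236 | 184 / 44 |
| 13, 5 | 0.382 | 0.864 | 0.442 | 92 / 41 |

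Over the whole grid, 3–38% score at least 15 and 45–92% at least 8. Of those who would qualify at 8 or more, 1 − 0.442 = 56% to 1 − 0.068 = 93% would be left out at 15.

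**7. Illustration of regression to the mean.** Expected untreated fall = (selected mean − population mean) × (1 − r), where for a normal score the bracketed difference is SD × φ(z)/(1 − Φ(z)). Assume mean 9, SD 4.5, retest correlation r = 0.6–0.8.

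- Cut 15: z = (14.5 − 9)/4.5 = 1.22; difference 4.5 × 0.189/0.111 ≈ 7.7; fall 7.7 × 0.2 to 7.7 × 0.4 = 1.5 to 3.1 points.
- Cut 8: z = (7.5 − 9)/4.5 = −0.33; difference 4.5 × 0.377/0.631 ≈ 2.7; fall 0.5 to 1.1 points.

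**The case against.** The best defence is that the harm arises only if 15 is applied to an undoubled sum. The figure 34+ itself points to a longer metric, so the screening software may double the score and work as intended, leaving only an incomplete range sentence. The article does not show which metric the system uses, so this may be right. It would shrink the fault to the text, but the article would then misstate the scale on which its outcome and SD are reported.

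Other points on that side stand and limit the claim:

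- A reader might infer that all but near-maximal stress scores are excluded. They are not: 15–21 is about the upper third of the possible values.
- A reader might infer that students below 15 are shut out of the study. The criteria are alternatives, so such a student can enter through PHQ-9 or GAD-7. What is lost is that student's contribution to the stress analysis.
- A reader might infer that the stress group cannot reach 35. A lower qualifying fraction means more screening, not impossibility.
- That the printed band generates the severity labels given to students is plausible but not stated.
- Cohen's d, the ANOVA F test and the 50% reduction rule do not change when every score is doubled. Jacobson–Truax results do not change either, provided all their inputs share one metric.
- Any baseline threshold in an uncontrolled study brings some regression to the mean. The literal reading adds to it; it does not create it.
- Symptom outcomes are to be treated as preliminary, and only one of three measures is affected.

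None of this reconciles a band reaching 34 with a scale ending at 21.

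**Conclusion.** Wrong as written. The stress cut-off and the stated scoring range cannot share a metric. The contradiction rests only on the article's own figures: 34 against a maximum of 21, with no conversion given. Because the cut-off also fixes which data are analysed, the Space from Stress analysis set is ambiguous for plain sums of 8 to 14 if the intended metric is 0–42, and that metric is an inference. On the literal reading, the range called mild to severe starts at 71% of the scale, the baseline SD is capped at about 3 points, and regression to the mean contributes more to the observed change.

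The percentages lost, screening numbers and regression figures depend on assumed means, SDs and correlations and serve only as illustration. Nor do the documents support a claim that participants have already been misclassified: the Trial status section reports 63 recruited, without a split by program or a description of how scores were computed. They also do not establish that 8 on the plain sum is the right threshold; that value only follows if doubling was meant.

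**What to change.** Reconcile the Eligibility criteria and Symptom outcome measures sections by stating a single scoring metric for the stress subscale. Use it for the cut-off, any severity bands fed back to students, and the reported outcome, including the SD and the Jacobson–Truax inputs. If the sum is doubled before the cut-off is applied, say so and give the resulting range; if it is not, restate the band so that it lies within 0–21. The choice belongs to the investigators.

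Then check which metric the online scoring applies, and re-derive stress analysis-set membership from item-level responses for those already recruited. Report the SD with its metric named, because an SD on 0–42 is twice that on 0–21.

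The cost is a short text correction, a check of the scoring code and a rescoring of stored item data. No additional participants are needed to make the correction. It is best done while recruitment is still open.

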### Interventions

#### Internet-delivered cognitive-behavior therapy (iCBT) programs

Space from Depression, Space from Anxiety, and Space from Stress are eight-module online CBT interventions, delivered on a Web 2.0 platform using media-rich interactive content (see Table 1 for a description of the Space from Depression program). Specifically, Space from Depression focuses on cognitive and behavioral components including self-monitoring and thought recording, behavioral activation, cognitive restructuring, and challenging core beliefs. Space from Anxiety includes problem solving strategies, collaborative empiricism, empowerment, and mindfulness. Space from Stress is primarily aimed at boosting positive well-being, addressing stress in university settings, and encouraging users to build a more balanced, enjoyable, and meaningful life. The content of the program modules follows evidence-based CBT principles. Each program is structured and incorporates introductory quizzes, videos, informational content, and interactive activities, as well as homework suggestions and summaries. In addition, personal stories and accounts from other users are presented. Participants will be encouraged to complete one module per week over 8 weeks [32], with weekly reviews provided by their supporter (10–15 min).

**Table 1 Tab1:** Overview of Space from Anxiety program

Module name	Brief description
Welcome to SilverCloud	Introduction to the program to orient users to the program’s structure and content. Invites users to consider their expectations of the program.
Getting Started	Outlines the basic principles of CBT and provides information about anxiety. Users are encouraged to begin to chart their own difficulties with anxiety.
Understanding Feelings	Focus on developing emotional literacy and understanding the connection between thoughts, feelings and behaviors. Explore different aspects of emotions, physical body reactions, anxiety and behavior, and the impact of lifestyle choices and purposeful relaxation on these domains.
Facing Your Fears	Highlights the importance of defining fears and introduces graded exposure strategy. Users can define a fear hierarchy and carry out experiments to gradually face their fears and reduce their anxiety. Encourages the user to accept their feelings and embrace uncertainty.
Spotting Thoughts	Identify anxious thoughts, and notice how they are typically accepted without question. Explore ways to disempower thoughts through balanced acceptance. Ideas are presented about how worry can perpetuate anxiety, and how some distraction strategies can be beneficial.
Challenging Thoughts	Challenge distorted thinking errors or patterns, and outlines helpful ways of thinking. Ideas around the identification of negative hot thoughts and the development of alternatives are also presented.
Bringing It All Together	Reflect on any change in perspectives that may have occurred and to plan for staying well. The important role of social support is outlined and set backs are normalized.

### SilverCloud platform

The SilverCloud platform was developed in Ireland by a multi-disciplinary team of clinical, design, and development professionals under the company name of SilverCloud Health. Delivered through the SilverCloud platform, the programs for the treatment of depression, anxiety, and stress employ several innovative engagement strategies for improving the user experience. These are divided into several categories: personal, interactive, supportive, and social.

#### Personal

Users have their own secure homepage and can fill in a profile with basic information about themselves. Along with establishing a sense of ownership, this information allows the supporter to provide more personal feedback. The homepage is intended to provide a reflective space; users can document their thoughts and feelings, and these can be elaborated on within the journal application, which also acts as the vehicle for therapeutic writing exercises. Users have actions suggested to them, and as they complete program modules, their achievements are noted. Users are free to access the modules in any order they wish, contributing to a sense of empowerment. Along with the central content, a range of satellite applications are provided, such as a goal-setting application that can be used independently of the program content. Applications are released as the user completes the modules, with the intention of maintaining engagement by introducing new features over time and not overwhelming the user initially.

#### Interactive

The program includes a number of interactive elements and graphical exercises aimed at engaging users with the therapeutic content (e.g., reflecting on their own thinking style). Users also have the ability to comment on content within the programs. Both exercises and comments can be explicitly shared with the supporter. The user is provided with immediate feedback wherever possible; for example, when a mood chart is completed, the application item is graphically updated on the home page.

#### Supportive

All users have an assigned supporter who provides weekly reviews of their progress in the program. This support is asynchronous; the supporter sets a date to review a user’s progress and does not provide feedback, support or contact outside this time. The supporter can support multiple users and can review the work of all their users within an allocated time period. Such asynchronous online contact may be logistically easier to implement for many services compared to, for example, motivational interviewing and telephone support. Users are encouraged to share their content (such as completed exercises and comments) with their supporter. This enables the supporter to respond in a more personal way and provide guidance and encouragement to keep using the program. Adherence information is also available to the supporters so they can keep track of the users’ progress. Because this information is personally sensitive, users can see the supporter’s view of their data. Making the visibility of user data to the supporter more transparent, and giving the user the ability to change the sharing status of data, provides the user with a greater sense of control.

#### Social

As one step to making the programs social, the user can see anonymous indications of other people in the system. The intention is to reassure users that they are not alone in experiencing difficulties and that many other people have experienced similar problems and overcome them. Users can respond to content by indicating that they “like” it, and can see how many other people liked it, helping to reduce the sense of isolation. Introducing contact with other users within any online system raises a number of ethical concerns regarding the possibility for unhelpful or negative content or communications. Thus, other more detailed shared content (such as tips and ideas) is subject to supporter moderation.

### Supporter’s role during treatment

Each participant will be assigned a supporter who will monitor the participant’s progress throughout the trial. Supporters will be professional staff at SCS, BMHC, or ISSS. Once participants choose a program, there will be a message from their supporter at their first login. This message welcomes them to the program, highlights aspects of the program, and encourages them in the use of the program. Each week, the supporters will log in and review participants’ progress, leaving feedback for them and responding to the work they have completed. The basic share level allows supporters to view users’ goals for the week, key messages, and progress points. If users wish to share more with their supporter, they can share journal entries. Participating supporters will receive training in the program and how to deliver feedback. Each supporter will provide post-session feedback of between 10 and 15 min per participant per session for their assigned participants. No adherence measure was developed to control for variance in the feedback provided as this natural variance between supporters reflects the expected variance in feedback found in a naturalistic setting.

### Measures

Acceptability data will include information acquired through the online SilverCloud system including data on usage and engagement. In addition, the satisfaction with treatment (SAT) measure will be completed at post-treatment, and finally, data from semi-structured interviews with participants will inform acceptability.

The Patient Health Questionnaire-9 (PHQ-9), the Generalized Anxiety Disorder-7 (GAD-7), the stress subscale of Depression, Anxiety, Stress Scale-21 (DASS-21), and a sociodemographic and history questionnaire will be completed at screening. The following measures, PHQ-9, GAD-7, and stress subscale of DASS-21 will be completed again 8 weeks after their initial log in or activation of the program and 3 months later. All data will be obtained through online self-reported measures.

### Sociodemographic information

The sociodemographic information and history questionnaire is based on the history questionnaire used in an earlier study [43]. It will be developed for the present study and will collect basic demographic information on the participants (e.g., age and gender) as well as information on any previous diagnosis of depression, anxiety, and stress disorders and on the length of time those symptoms were experienced; participants’ experiences of counseling, therapy, and medication for depression, anxiety, and stress; previous diagnosis of an organic mental health disorder such as schizophrenia, psychosis, or bipolar disorder; and items related to the presence of psychosis, alcohol and drug misuse, and/or any recent medical diagnosis.

### Symptom outcome measures

The PHQ-9 [26, 50] is a 9-item self-report measure of depression that has been widely used in screening, primary care, and research. The PHQ-9 items reflect the diagnostic criteria for depression outlined in the *Diagnostic and Statistical Manual of Mental Disorders, Fourth Edition–Text Revision* (DSM–IV–TR) [3]. Items are rated on a 0 to 3 scale. Summed scores range from 0 to 27; higher scores reflect a greater severity of depressive symptoms [26, 50].

The GAD-7 [49] comprises 7 items measuring symptoms and severity of GAD based on the DSM-IV diagnostic criteria for GAD. The GAD-7 has good internal consistency (.89) and good convergent validity with other anxiety scales. Items are rated on a 0 to 3 scale. Summed scores range from 0 to 21; higher scores indicate greater severity of symptoms [49].

Stress subscale of Depression, Anxiety and Stress scale-21 (DASS-21). The DASS-21 [28] is an abbreviated version of the original 42-item DASS. It is composed of three 7-item subscales measuring symptoms of depression, anxiety, and stress. Participants will be asked to rate the degree to which they endorse each of the seven stress items on a 4-point scale (0 to 3). Summed scores range from 0 to 21; higher scores indicate greater severity of symptoms. Scores on the DASS-21 have been found to be valid measures of depression, anxiety, and stress in non-clinical samples [17].

